## Data collection

4

Participants are reviewed at face-to-face assessments at recruitment. If a participant is unable to attend a face-to-face assessment, a person with legal responsibility will be a substitute. A secondary review of all ALI cases and a random sample of non-ALI cases will be performed by an independent expert investigator who is blinded to the initial ALI adjudication. The following data will be collected through the assessments:

### Demographics and etiology

4.1

Height, weight, the body mass index (BMI), regular use of prescription drugs (include antihypertensive agents, hypoglycemic agents or insulin, anticoagulant, and nonsteroidal anti-inflammatory drugs), smoking history (age commenced, age ceased, and average cigarettes smoked per day), hypertension history (age of onset and treatment), and diabetes history (age of onset and treatment) will be recorded at recruitment.

### Preoperative assessment

4.2

#### Time from onset of symptoms to surgery

4.2.1

The onset time of sudden severe chest or upper back pain (often described as a tearing, ripping, or shearing sensation that radiates to the neck or down the back), loss of consciousness, shortness of breath, sudden difficulty speaking, loss of vision, weakness or paralysis of 1 side of the body will be recorded.

#### Hemodynamics

4.2.2

The invasive blood pressure will be recorded as a baseline immediately after the left radial artery catheter.

#### Echocardiogram

4.2.3

The data of preoperative echocardiogram will be recorded, including aortic diameter, LVEF, and left ventricular end-diastolic dimension (LVEDd).

#### Operative risk assessment

4.2.4

In this prospective study, each participant will be assessed with the European system for cardiac operative risk evaluation (EuroSCORE).

#### Murray lung injury score assessment

4.2.5

After routinely anesthesia and tracheal intubation, based on a FiO_2_ of 100%, a PEEP of 5 cmH_2_O, a tidal volume of 8 mL/kg, a 1:2 of inspiratory/expiratory ratio, and a respiratory rate of 10 per minute, the Murray LIS is obtained by radiographic findings on admission, oxygenation index (a PaO_2_/fraction of FiO_2_ ratio), lung compliance, and PEEP value.^[12,13]^

### Surgical data

4.3

The durations of surgery, CPB and aortic cross-clamping, and lowest temperature during CPB will be recorded. The blood transfusion, intravenous colloid, and crystalloid volumes and uine volume during surgery will also be noted.

### Postoperative data

4.4

During a 24-hour postoperative period, the blood transfusion, intravenous colloid, and crystalloid volumes and uine volume will be calculated. The duration of postoperative mechanical ventilation and in-hospital mortality will also be recorded.

### Serum measurements

4.5

A 10-mL venous blood sample will be drawn from central vein catheter immediately after tracheal intubation. After rapidly centrifugation, plasma will be obtained and stored immediately at −70 °C condition for further analysis. Plasma levels of interleukin-6, interleukin-10, tissue factor, tissue factor pathway inhibitor, plasminogen activator inhibitor type 1, human leukocyte elastases, tumor necrosis factor α, vascular endothelial growth factor, prostaglandin I2, and thromboxane B2 will be assayed by enzyme-linked immune absorbent assay according to the manufacturer's specification (MULTISKAN MK3 Automatic microplate reader, Thermo Fisher Scientific Inc, Waltham, MA). Methane dicarboxylic aldehyde, myeloperoxidase, total antioxidation capacity, and total superoxide dismutase will be determined by ultraviolet spectrophotometry. The platelet count, Hb, white blood cells, glucosamine, lactic acid, troponin, fibrinogen (FIB), FIB degradation product, d-dimer, active part thrombin time, and prothrombin time will be determined by standard quantitative assay techniques in the hospital Clinical Laboratory Center.

## Statistical analysis

5

The data obtained in this study will be analyzed using SPSS 18.0 (SPSS Inc., Chicago, IL). Univariate and multiple logistic regression analyses will be used to determine the independent predictors of preoperative ALI. Univariate analysis will be applied for demographic data (age, sex, and BMI), comorbidities (smoking history, hypertension, and diabetes), preoperative data (hemodynamics, onset of symptoms to surgery, aortic diameter, LVEF, LVEDd, and EuroSCORE), surgical data (surgery time, hypothermic circulatory arrest time, intravenous colloid, crystalloid, and transfusion volumes), postoperative variables (intravenous colloid, crystalloid and transfusion volumes, urine volume, seroma volume of drainage, mechanical ventilation time, and in-hospital mortality), and serum measurements before surgery (coagulation/fibrinolysis, inflammatory, ROS, platelet, and endothelial cell function). In univariate analysis, variables associated with preoperative ALI with a *P* value <0.10 will be selected. Then, these selected variables will be put into the multiple logistic regression analysis to identify the independent predictors of preoperative ALI.

Receiver operating characteristic curve will be used to test discrimination of multivariate regression model and to determine the cutoff value in predicting preoperative ALI with sensitivity and specificity, respectively. The missing values will be displaced by means according to Intention-To-Treat rules. A *P* value <0.05 will be considered statistically significant.

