## Background

1

Patients presenting with aortic dissection within 2 weeks of the onset of symptoms are considered to have acute aortic dissection (AAD).^[1]^ AAD is a severe cardiovascular disease demonstrating the characteristics of acute onset and rapid development, with high morbidity and mortality. It has been shown that mortality of patients with AAD per hour early after the onset of symptoms is about 1% to 2%. Furthermore, mortality of patients with AAD who do not receive surgery is 58.0% in contrast to 26% in surgically treated patients.^[2,3]^ In patients with AAD, multiple organ failure including acute lung injury (ALI) is frequent.^[4,5]^ It is reported that 51% of patients meet the criterion of oxygenation impairment (oxygen fraction [PaO_2_/FiO_2_] ≤ 200 mm Hg) within 24 hour after onset of distal type AAD.^[6]^ Actually, preoperative ALI has been shown as a frequent complication associated with a number of untoward consequences, such as prolonged ventilator support, longer stay in intensive care unit and hospital, and even induces death. The previous work by Wang et al^[7]^ showed that the incidence of postoperative hypoxemia was up to 49.5% in Chinese adult patients undergoing Stanford type-A AAD surgery and postoperative hypoxemia was attributable to preoperative disturbance in oxygenation (78.5%, PaO_2_/FiO_2_ ≤ 200 mm Hg). In addition, preoperative hypoxemia can also result in surgery delay, which increases the risk of aortic rupture, cardiac tamponade, or even death. Therefore, the prophylaxis and/or treatment of preoperative ALI induced by AAD is important for final outcomes of patients.

Better understanding of the pathophysiology of preoperative ALI in the patients with AAD can improve clinical prophylaxis and/or treatment, but its underlying molecular and cellular mechanisms remain largely unknown. It is reported that the occurrence of oxygenation impairment on hospital days 2.5 in patients with Standford type-B AAD can be predicted by a multivariate logistic regression model.^[8]^ To our best knowledge, however, there is no study having assessed whether the preoperative ALI in Chinese adult patients undergoing the Standford type-A AAD surgery can be predicted by preoperative clinical and basic assessments. Thus, we put forward a prospective study strategy aiming to address the above issues.

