### Participants (inclusion and exclusion criteria)

3.2

The sample of subjects is estimated to 130 patients, based on a 79% incidence of ALI before surgery in patients with Stanford type-A AAD^[7]^ and the set power to 80% for a type I error of 5% (Power Analysis and Sample Size, PASS V11.0, NCSS, LLC. Kaysville, UT). A convenient sample will be recruited from the Beijing Anzhen Hospital. The AAD surgery in the Beijing Anzhen Hospital is performed in approximately 300 cases per year. If 30% of these patients are eligible and consent, we will meet our recruitment target in about 1.5 years, which can avoid the bias from the different levels of surgical procedures in different periods.

Patients aged 18 to 75 years will be included. The patients with coronary heart disease; heart failure; severe cardiac tamponade; unstable hemodynamics; nervous system abnormalities; clinically apparent malperfusion^[9]^ including lower limb, cerebral, coronary, and renal malperfusion; and visceral ischemia will be excluded. All patients enrolled in this study have normal hepatic and renal function according to the preoperative physical and laboratory examinations. No patient is prescribed with nonsteroidal anti-inflammatory drugs or corticosteroids before or after admission. All patients will be informed and consented with regard to their participation in the study.

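### Ordinary logistic regression with about 27 non-ALI patients will, on average, overstate the adjusted odds ratios, modestly in the likely range of 5 to 11 entered variables

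*Protocol article*

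**What the plan says.** Section 5 of the protocol article names the method, the software and the entry rule. The method: "Univariate and multiple logistic regression analyses will be used to determine the independent predictors of preoperative ALI". The software: "The data obtained in this study will be analyzed using SPSS 18.0". The entry rule: "variables associated with preoperative ALI with a *P* value <0.10 will be selected", after which "these selected variables will be put into the multiple logistic regression analysis to identify the independent predictors of preoperative ALI". It mentions no penalty, shrinkage, small-sample correction or cap on the number of variables.

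Section 3.2 fixes the size: "The sample of subjects is estimated to 130 patients", "based on a 79% incidence of ALI before surgery in patients with Stanford type-A AAD". Sections 4.5 and 5 together list about 49 candidates: 3 demographic, 3 comorbidity, 6 preoperative, 5 surgical, 7 postoperative and 25 laboratory.

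**The concern.** In logistic regression the information is limited by the smaller outcome group, which here is the patients without ALI. When that group is small relative to the number of variables, maximum-likelihood log odds ratios are biased away from zero. This is a property of the estimator. It affects genuine predictors and would remain if the screening step chose perfectly. It is therefore a different problem from false-positive screening or an optimistic ROC curve.

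Identifying independent risk factors is a stated aim (section 2), and the Discussion expects the adjusted analysis to shed light on mechanisms. Adjusted odds ratios that are systematically too far from 1 would overstate how strongly coagulation, inflammation or other markers relate to preoperative ALI.

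**Working it through.** **The plan's own figure.** The sample size of 130 cannot be reproduced. Section 3.2 gives incidence, power and type I error, but no effect size, null value or sidedness. For example, a two-sided one-sample test of 0.68 against 0.79 gives 131, but the 0.68 has to be assumed. This does not affect the present point, which needs only the total and the incidence.

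**Size of the smaller group.** 130 × (1 − 0.79) = 27.3 non-ALI patients. With the 78.5% in the Background, 130 × 0.215 = 27.95.

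**Number of variables entered.** 49 × 0.10 = 4.9 would pass the screen by chance if none mattered. Simulating the screen with 49 candidates, and with 37 (the list less its 5 surgical and 7 postoperative items), with 3 to 5 true predictors at OR 1.5 or 2.0, gave a median of 5 to 11 entered. That is 27.3/5 = 5.5 down to 27.3/11 = 2.5 non-ALI patients per variable.

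**Estimators.** Maximum likelihood solves Σ(yᵢ − pᵢ)xᵢⱼ = 0. Firth solves Σ[yᵢ − pᵢ + hᵢ(½ − pᵢ)]xᵢⱼ = 0, where hᵢ is the leverage. This removes the leading term of the small-sample bias.

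**Simulation 1: every entered variable genuine, no selection.** N = 130, 79% ALI, standard-normal predictors, true OR 2.0 per SD, 1000 runs per row. Entries are mean log OR / true log OR, with the corresponding OR in brackets (2.0 raised to the ratio, e.g. 2.0^1.107 = 2.15).

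| Variables | Non-ALI per variable | ML, uncorrelated | ML, correlation 0.3 | Firth, both |
|---|---|---|---|---|
| 1 | 27.3 | 1.036 (2.05) | 1.050 (2.07) | 1.000–1.013 |
| 3 | 9.1 | 1.070 (2.10) | 1.065 (2.09) | 0.995–1.005 |
| 5 | 5.5 | 1.107 (2.15) | 1.129 (2.19) | 1.002–1.007 |
| 8 | 3.4 | 1.170 (2.25) | 1.281 (2.43) | 0.994–0.999 |
| 10 | 2.7 | 1.225 (2.34) | 1.484 (2.80) | 0.994–1.008 |

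The 2.80 is an extreme setting (ten correlated predictors, each doubling the odds), in which 62 of 1000 ML fits were not estimable. With true OR 1.5 the ML ratio is 1.09 at 5 variables and 1.16–1.27 at 10.

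**Simulation 2: a few genuine predictors plus null variables.** With three genuine predictors at OR 2.0 the ML ratio is 1.10 at 5 variables (OR 2.14), 1.14 at 8 (2.20), 1.17 at 10 (2.25) and 1.29 at 15 (2.45). At N = 1300 the ML ratio is 1.01, so this is small-sample bias. With four genuine predictors and correlation 0 to 0.4, the mean ML odds ratio is 2.16–2.21 at 6 variables, 2.25–2.35 at 10, 2.38–2.61 at 14 and 2.63–2.95 at 18. Firth gives 1.99–2.03 throughout. At 10 variables the root mean squared error of the log OR is 0.36–0.54 for ML and 0.28–0.40 for Firth.

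**Simulation 3: inference and discrimination at 5 to 11 variables.** ML coverage is about 0.94–0.96 (0.932–0.958 in one set of runs) and type I error for null variables about 4–6%. At 18 variables ML coverage falls to about 0.91 and type I error rises to 7–8%. Out-of-sample AUC was the same to three decimals for both estimators from 5 to 18 variables.

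**Sensitivity to incidence, 10 variables.** At 60% ALI the ML odds ratio is 2.19–2.22. At 85% (130 × 0.15, about 20 non-ALI) it is 2.35–2.52.

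**The case against.** The strongest case against concedes the direction and disputes the consequence.

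- **The document never mentions an odds ratio or a confidence interval.** It speaks of identifying predictors and of a ROC curve. This stands: odds-ratio reporting is a reasonable expectation from a multivariable logistic model, but it is inferred.
- **The bias is modest against the noise.** At 5 to 11 variables it is 0.07–0.19 on the log scale, against a sampling SD of 0.31–0.54. This also stands, and it limits the importance of the point.
- **Firth costs power.** With Wald tests at 11 variables, power fell from 0.77 to 0.71 (uncorrelated) and from 0.50 to 0.43 (correlated). With profile-likelihood tests the loss against ML Wald tests is only 0–4 points, so most of this objection falls away.
- **The estimator may be left to an unseen analysis plan.** The article does state a method, a package and an entry rule, and read plainly these mean unpenalised maximum likelihood. A fuller plan could add a correction.
- **The 27 is only a planning figure.** The Background ties the 78.5% to a PaO2/FiO2 of 200 mm Hg or less, whereas section 3.5 grades ALI by the Murray score, with only a score of 0 counted as none. The true count could move either way.

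A reader might infer that the confidence intervals will too often miss the truth, or that false-positive predictors will follow from the estimator. The planned rule does not support that: those failures appear at about 14 or more variables, beyond the median of 5 to 11 that the screen produced. A reader might also infer that this trial's odds ratios will certainly be too large. They will not: 51–63% of single estimates exceeded the truth.

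**Conclusion.** The point holds as a statement about average bias. As written, section 5 uses an estimator that overstates adjusted odds ratios on average. A true 2.0 becomes about 2.1–2.2 with 5 variables and about 2.2–2.4 with 8–11, and more if more enter, which the plan does not prevent. With 1–3 variables the bias is only 4–8% on the log-odds scale. It is not a failure of interval coverage, type I error or discrimination in the likely range.

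This rests on four assumptions: about 79% incidence; unpenalised maximum likelihood as the meaning of the stated method; odds ratios of 1.5–2.0 per SD; and 5–11 variables entered. It is worth correcting because Firth lowers both bias and root mean squared error on the same data. It is not the main weakness of the modelling strategy: after the P<0.10 screen at true OR 1.5, Firth estimates were still inflated by 18–22% on the log scale (ML 36–37%).

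**What to change.** In section 5, state that the multivariable model will be fitted by Firth-penalised logistic regression, with penalised profile-likelihood 95% confidence intervals and tests. If predicted probabilities are reported, and not only the ROC curve, state that the intercept will be corrected.

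The cost is one or two sentences, free software in place of the standard SPSS routine, slightly less striking odds ratios and 0–4 points of power. The change does not deal with the selection bias from the uncapped P<0.10 screen. That needs a separate remedy; fewer candidates would also shrink the bias described here.

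### Twelve surgical and postoperative variables, including ventilation time and in-hospital death, are candidate predictors of an ALI status already scored before they exist

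*Protocol article*

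**What the plan says.** Section 5 (Statistical analysis) names the purpose: "Univariate and multiple logistic regression analyses will be used to determine the independent predictors of preoperative ALI". It then lists the candidates for univariate analysis. Besides demographic, comorbidity, preoperative and serum items, the list contains "surgical data (surgery time, hypothermic circulatory arrest time, intravenous colloid, crystalloid, and transfusion volumes" and "postoperative variables (intravenous colloid, crystalloid and transfusion volumes, urine volume, seroma volume of drainage, mechanical ventilation time, and in-hospital mortality".

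The selection rule applies to the whole list. Any variable with P<0.10 is carried into the multiple logistic regression, whose stated purpose is to find independent predictors of preoperative ALI. An ROC curve then tests that model's discrimination and supplies a predictive cutoff. No sentence exempts the surgical or postoperative variables.

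Section 4.2.5, which sits under the heading Preoperative assessment, sets when the outcome is determined: "After routinely anesthesia and tracheal intubation, based on a FiO_2_ of 100"% and fixed ventilator settings, "the Murray LIS is obtained by radiographic findings on admission, oxygenation index", compliance and PEEP.

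Section 1 (Background) associates preoperative ALI with "untoward consequences, such as prolonged ventilator support, longer stay in intensive care unit and hospital, and even induces death". It frames the research question as prediction from preoperative information.

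**The concern.** A predictor must have its value before, or at the latest when, the outcome is determined. Surgery time, circulatory arrest time, fluid and transfusion volumes, drainage, ventilation time and in-hospital death have no value yet when ALI is scored. Any association they show with preoperative ALI runs from ALI to the variable, or comes from a shared cause. It cannot run the other way.

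Three things are at stake. The final model may name consequences of ALI as its independent predictors. Adjusting for those consequences may shift the odds ratios of the true preoperative factors. And the ROC cutoff would need inputs that do not exist before surgery, so it could not serve the prophylaxis and treatment purpose in section 2 (Aims).

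**Working it through.** The plan gives no figure of its own on this point. The check is a comparison of timing, a count, and an illustration of what the selection rule does.

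**1. Timing.**
- Outcome: scored after intubation, from the admission radiograph and the first controlled ventilator settings (section 4.2.5).
- Demographic, comorbidity and preoperative items: known by then.
- Serum sample: drawn immediately after intubation (section 4.5), so essentially concurrent with scoring.
- Surgical items: arise during the operation (section 4.3).
- Postoperative items: arise afterwards (section 4.4).

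**2. Count from the section 5 list, with haemodynamics taken as one item.**
- Known by scoring: 3 demographic + 3 comorbidity + 6 preoperative = 12.
- After scoring: 5 surgical + 7 postoperative = 12.
- Non-serum total: 12 + 12 = 24, so 12/24 = 50% follow the outcome.

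**3. Chance selection alone.** If none of the 12 were associated with ALI and they were independent, the probability that at least one passes P<0.10 is 1 − 0.9^12 = 0.72, with 12 × 0.10 = 1.2 expected.

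**4. Selection when the variable is an effect of ALI (simulation, assumed effects).** There were 130 patients and 1,500 runs per setting. One true preoperative predictor x is standard normal, with logit P(ALI) = 1.5 + 0.7x (about 80% ALI). One later variable is v = e × ALI + standard normal noise, so it is caused only by ALI.

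| Assumed shift e (SD) | Passes P<0.10 | Also P<0.05 with x in the model | Mean apparent AUC, x alone | Mean apparent AUC, x and v |
|---|---|---|---|---|
| 0 | 9% | 4% | 0.68 | 0.69 |
| 0.3 | 38% | 24% | 0.68 | 0.71 |
| 0.5 | 72% | 56% | 0.68 | 0.73 |
| 0.8 | 97% | 92% | 0.68 | 0.78 |

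The last column fits both variables in every run, whether or not v was selected.

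**5. Effect on the preoperative odds ratios.** Let v = e × ALI + c × x + unit-variance normal noise, and logit P(ALI | x) = a + b × x. By Bayes' rule, logit P(ALI | x, v) = a + b × x + e × (v − c × x) − e²/2. The coefficient of x becomes b − e × c, and v receives coefficient e. If v depends on ALI alone (c = 0), x keeps its coefficient and v still appears as a predictor. If v also depends on x, the log odds ratio of x is shifted by e × c. In-hospital death, which plausibly depends on age or EuroSCORE as well as on ALI, would be such a variable.

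**6. Room in the model.** At the 79% incidence in section 3.2, 130 × 0.79 = 102.7 and 130 × 0.21 = 27.3. That is about 103 patients with ALI and 27 without, which leaves little capacity for terms that do not belong.

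**The case against.** One defence is that the list describes ALI and non-ALI patients, and that an unseen analysis plan limits the multivariable model. The text does not allow this. It states both the list and the rule that sends every screened-in variable to the predictor model, so this is a rule fixed in the article and not a detail left open. Collecting the later variables is proper; their use as predictors is the fault.

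Other objections stand and limit the point:
- A reader might infer that the protocol expects ventilation time and death to be strongly associated with ALI. The Background says only that they are associated and gives no effect size. The simulated shifts are assumptions.
- The 0.72 assumes independence, which is doubtful for overlapping fluid and transfusion volumes, and it would apply to any 12 candidates.
- A reader might infer that the later variables displace true preoperative factors. No stepwise rule or cap is stated; all selected variables enter together. The harm is distortion and overloading.
- A share of all candidates cannot be given firmly, because section 5 names serum candidates by group and not by assay.
- Scoring before incision is a reasonable reading of section 4.2.5 and of the label preoperative, but it is not stated in words.
- A reader might class onset-to-surgery time with the post-outcome variables because "preoperative hypoxemia can also result in surgery delay". But ALI is scored at intubation for surgery, so this interval is essentially known by then and is a legitimate measure of disease duration. Reverse influence is possible, which calls for caution and not exclusion.

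**Conclusion.** The point holds for the 12 surgical and postoperative variables. The rule in section 5, followed literally, can present effects of preoperative ALI as its independent predictors, can bias the adjusted odds ratios of preoperative factors that also influence those variables, and yields a model and cutoff unusable before surgery. It also conflicts with the causal direction and the research question in the Background.

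This conclusion rests on time order alone. The simulated rates illustrate the mechanism under assumed effects and are not forecasts.

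The scope is the predictor and ROC analysis. A reader might infer that the whole study is compromised. The documents do not support that: the incidence aim, the sample size and the data collection are untouched, and the data for a correct model are already being collected.

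**What to change.** In section 5, restrict the candidates for the ALI model and for the ROC analysis to variables known by the time ALI is scored: the demographic items, the comorbidities, all six listed preoperative items (including haemodynamics and EuroSCORE), and the measurements from the blood sample drawn at intubation.

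Move the five surgical and seven postoperative variables to a separate analysis in which they are outcomes compared by preoperative ALI status.

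Keep onset-to-surgery time as a candidate, with a note that hypoxaemia may lengthen it. Interpret its association with caution, or repeat the model without it as a sensitivity analysis.

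The cost is rewriting one paragraph. The 130 patients and the data to be collected stay the same.

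### The planned ROC analysis gives only apparent performance, so the reported AUC and specificity, and to a lesser degree sensitivity, will be too high

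*Protocol article*

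**What the plan says.** Section 5 (Statistical analysis) sets out a sequence. Demographic, comorbidity, preoperative, surgical, postoperative and serum variables are tested one at a time, and "variables associated with preoperative ALI with a *P* value <0.10 will be selected". Next, "these selected variables will be put into the multiple logistic regression analysis to identify the independent predictors of preoperative ALI". The performance step follows: "Receiver operating characteristic curve will be used to test discrimination of multivariate regression model and to determine the cutoff value in predicting preoperative ALI". The cut-off is to be accompanied by its sensitivity and specificity. Missing values are replaced by means.

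Section 3.2 (Participants) describes one set of patients: "The sample of subjects is estimated to 130 patients". That size is said to be "based on a 79% incidence of ALI before surgery in patients with Stanford type-A AAD". On the source of the patients the section says: "A convenient sample will be recruited from the Beijing Anzhen Hospital".

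The article mentions no second cohort, data split, cross-validation, bootstrap or shrinkage. The blinded secondary review in section 4 (Data collection) concerns the adjudication of ALI, not the model.

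**The concern.** A ROC curve drawn on the patients who supplied the model does not test it. The same data choose the variables, estimate the coefficients and place the cut-off, and each step adapts to chance features of those patients. The resulting AUC, sensitivity and specificity describe fit to this sample and overstate what the model would do in the next patients.

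The problem is sharp here because the candidates are many and the non-ALI group is small. The Background presents the study as asking whether preoperative ALI can be predicted from preoperative assessments, and the ROC result is the only evidence on predictive ability that the article names. The incidence estimate is not affected.

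**Working it through.** **The plan's own figures.** The article states no AUC, sensitivity or specificity, so there is none to reproduce. The sample size of 130 cannot be derived from 79%, 80% power and 5% alone, because no null value or precision is given. A 95% interval of ±7 points would give 1.96² × 0.79 × 0.21 / 0.07² = 130.1, so 131, but that half-width is not in the article. I take 130 as given; the point does not depend on its origin.

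**Inputs from the article.**
- With ALI: 130 × 0.79 = 102.7, about 103. Without: about 27.
- Clinical candidates (section 5): 3 demographic + 3 comorbidity + 6 preoperative (hemodynamics counted once) + 5 surgical + 7 postoperative = 24.
- Blood analytes (section 4.5): 10 by ELISA + 4 by spectrophotometry + 11 in the hospital laboratory = 25.
- Total: 24 + 25 = 49. Without surgical and postoperative variables: 49 − 12 = 37.
- Patients of the rarer class per candidate: 27 / 49 = 0.55.
- Pure-noise variables expected to pass the screen: 49 × 0.10 = 4.9.

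**Assumptions not in the article.** True signal, correlation among candidates, and whether the final model keeps all screened variables or only those with P<0.05. These were varied.

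**Simulation.** Each run draws 130 patients at 79% prevalence with normal covariates, screens at P<0.10, fits the logistic model, and takes the AUC and the best (Youden) cut-off on the same data. The frozen model and cut-off are then scored on 20,000 new patients. There were 400 runs per scenario. Optimism = apparent value − value in new patients.

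With 49 independent candidates and all screened variables kept:

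| True signal | AUC, apparent vs new | Optimism | Specificity | Sensitivity |
|---|---|---|---|---|
| none | 0.76 vs 0.50 | 0.26 | 0.75 vs 0.39 | 0.71 vs 0.61 |
| two weak predictors | 0.81 vs 0.58 | 0.23 | 0.79 vs 0.45 | 0.75 vs 0.66 |
| four predictors | 0.84 vs 0.63 | 0.20 | 0.79 vs 0.47 | 0.78 vs 0.70 |
| five strong predictors | 0.90 vs 0.76 | 0.14 | 0.86 vs 0.59 | 0.83 vs 0.77 |

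Specificity is overstated by 0.36, 0.34, 0.32 and 0.27, and sensitivity by 0.10, 0.09, 0.08 and 0.06. In the first row, sensitivity + specificity − 1 is 0.71 + 0.75 − 1 = 0.46 apparent and 0.61 + 0.39 − 1 = 0 in new patients.

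Range of AUC optimism over the four signal levels:

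| Candidates | Correlation | All screened kept | Only P<0.05 kept |
|---|---|---|---|
| 24 | 0 | 0.08 to 0.18 | 0.08 to 0.12 |
| 37 | 0 | 0.11 to 0.22 | 0.10 to 0.16 |
| 49 | 0 | 0.14 to 0.26 | 0.11 to 0.18 |
| 24 | 0.3 | 0.09 to 0.15 | 0.05 to 0.07 |
| 37 | 0.3 | 0.12 to 0.18 | 0.01 to 0.07 |
| 49 | 0.3 | 0.15 to 0.21 | 0.00 to 0.08 |

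The near-zero entries (0.005 and 0.001) come from strong, correlated signal, where on average only 0.7 and 0.1 variables survived P<0.05. Runs with an empty model score 0.50 on both sides and dilute the mean. With many correlated strong predictors and all screened variables kept, the fit approaches separation, so those cells are numerically unstable. A second simulation gave about 0.02 to 0.10 for correlated candidates with only P<0.05 kept, and about 0.09 to 0.22 with real signal and all screened variables kept.

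**The case against.** The strongest reply is that this is an omission. A journal article condenses the plan, internal validation is often described elsewhere, and a ROC curve is a legitimate tool. Part of this stands: the article never says that the ROC step uses the same patients, and an analysis plan not shown could add a correction. But the objection here is to a stated procedure. The article names the method that will test discrimination and set the cut-off, places it directly after the fitted model, and describes only one sample. Followed as written, it gives a biased result.

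The second reply concerns size, and much of it stands. The largest figures assume no true predictor and a model that keeps every screened variable. The article offers a biological rationale for the inflammation and coagulation markers, some of which are likely to be correlated, and its 5% significance level may serve as the final retention rule. In that setting the bias is small. The count of 49 is also an upper figure: hemoglobin, lactic acid, troponin and glucosamine do not clearly belong to the serum classes named in section 5, and dropping them leaves 45.

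Third, the Aims (section 2) list incidence, risk factors and mechanisms, not a prediction tool, and no clinical use of the cut-off is stated. That limits the consequence but does not remove the bias from the figures to be reported.

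**Conclusion.** The point holds in direction, and in size as a range. AUC optimism is about 0.08 to 0.26 if all screened variables are kept, and about 0.02 to 0.10 if candidates are correlated and only P<0.05 variables stay. Real signal does not remove it: five strong predictors among 49 independent candidates still give 0.90 against 0.76. The conclusion rests on same-sample evaluation, which is inferred from the single cohort described, and on the assumed signal, correlation, candidate count and retention rule.

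A reader might infer two stronger claims that the documents do not support:
- **That AUC, sensitivity and specificity are all substantially inflated.** This fits AUC and specificity when all screened variables are kept, but the sensitivity error is mostly 0.05 to 0.10.
- **That a worthless model will look clinically useful.** The 0.76 against 0.50 describes only the case of no true predictor with 49 candidates, and the article gives no basis for taking that case as the expected one.

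This should be corrected before the prediction results are reported. It does not threaten the incidence aim.

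**What to change.** In section 5, make the optimism-corrected AUC, sensitivity and specificity the primary performance figures, and show the apparent values only beside them. Obtain the correction from a bootstrap, for example 500 resamples. In each resample, repeat the imputation, the P<0.10 screen, the model fit under the stated retention rule, and the choice of cut-off. Score that model and cut-off in the resample and in the original 130 patients, average the differences, and subtract the average from the apparent values. This requires section 5 to say whether the final model keeps all screened variables or only those with P<0.05.

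A split sample is a poor substitute: half of about 27 non-ALI patients is 13 or 14. A calibration slope and shrinkage of the coefficients are optional. Uniform shrinkage keeps the ranking of patients, so it does not correct the AUC.

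The cost is a few hours of analysis, no new data, and a lower headline AUC.
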